### 2.5. Statistical Analysis

Sample size (286 kids in each arm of the study) was estimated using the “two independent means” approach, assuming an effect size of 0.75 BMI units (SD = 1.5), 80% power, *α* = 0.05 (two‐tailed), and an expected attrition rate of 15%. The effect size of 0.75 BMI units was selected based on a balance between clinical relevance and the practical limitations of our study. Given that our sample was limited to children who volunteered to participate, a larger sample was not feasible. Therefore, we opted for an effect size of 0.75 BMI units, which we considered both clinically meaningful in the context of pediatric obesity prevention [22, 24] and achievable within the constraints of our available sample size. Statistical analyses were performed using STATA version 14MP (StataCorp LLC, College Station, TX, USA).

Although the sample size calculation was initially performed at the individual level using a two independent means approach, we acknowledge that the cluster‐randomized design requires consideration of intracluster correlation (ICC). The absence of this adjustment may have led to an overestimation of statistical power, and this is recognized as a limitation. To appropriately account for clustering, all outcome analyses will be conducted using statistical models that consider the hierarchical structure of the data, with children nested within schools. Specifically, mixed‐effects regression models (or cluster‐robust standard errors) will be used to adjust for school‐level clustering.

In the descriptive statistical study, means, minimum and maximum values, and SD were calculated for quantitative variables. For qualitative variables, counts and proportions are presented. The 95% confidence interval for mean values and proportions was calculated. The hypothesis test for comparing proportions was used to verify the difference between proportions and the Student’s *t*‐test or Mann–Whitney test (if the distribution was not normal) was used to analyze differences between means of two samples. In the case of more than two samples, the tests applied were ANOVA or Kruskal–Wallis (non‐normal samples). Significant differences were considered when *p* < 0.05. Pearson correlation coefficient was used to evaluate the existence of correlation between average moderate/vigorous physical activity per day and BMI. Outcome assessors were blinded to school allocations to ensure unbiased evaluation of results.

At the end of the study, the primary and secondary outcomes will be reassessed. The primary analysis will be conducted according to the intention‐to‐treat (ITT) principle, where all randomized participants will be analyzed according to their assigned treatment group, regardless of adherence or withdrawal. Missing data will be handled using multiple imputation techniques. The treatment effect for each outcome will be estimated using appropriate statistical models, adjusting for baseline values of the outcome and other relevant covariates. Multivariate linear and logistic regression models will be used to evaluate intervention effects, adjusting for baseline covariates such as age, sex, and school type. Interaction terms will explore effect modification by SES and baseline BMI category. All multivariate analyses will adjust for school type as a proxy for SES, given its known association with childhood obesity and its imbalance between study arms. No changes to the methodology were implemented after trial commencement.

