## 3. Results

A total of 557 children from 13 schools participated in the study, 298 in the intervention group (from 5 schools) and 259 in the control group (from 8 schools). As anticipated in our methodology, achieving a 1:1 ratio of participants resulted in an unequal number of schools between the intervention and control groups due to variations in class sizes. This outcome was consistent with our randomization protocol, which prioritized participant balance over school number balance.

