### 3.1. Anthropometry

Table 2 shows the characteristics of the participants.

**TABLE 2 tbl-0002:** Anthropometric characteristics in the pre‐intervention situation.

	Control (*N* = 259)			Intervention (*N* = 298)			*p*‐values
	*N*	Mean (%)	SD	*N*	Mean (%)	SD	
School type	8			5			
Public	87	33.6%	n/a	121	40.6%	n/a	0.063
Partially subsidized	120	46.3%	n/a	109	36.6%	n/a	
Private	52	20.1%	n/a	68	22.8%	n/a	
Sex^∗^ (girls)	155	59.8%	n/a	152	51%	n/a	0.036^∗^
Age^∗^ (years)		8.1	1.3		7.6	1.2	0.000^∗^
Height^∗^ (cm)		133.2	9.8		130.7	8.5	0.002^∗^
Weight (kg)		31.8	9.7		30.6	8.5	0.125
Body mass index (kg/m^2^)		17.6	3.4		17.6	3.2	0.957
Weight *z*‐score							
Normal (0)	170	65.6%	n/a	176	59.1%	n/a	0.245
Overweight (+1)	47	18.2%	n/a	60	20.1%	n/a	
Obesity (+2)	42	16.2%	n/a	62	20.8	n/a	
Triponderal body index		13.2 kg/m^3^	2.2		13.5 kg/m^3^	2.1	0.129
% of body fat		21.8%	7.1		22.8%	6.8	0.092
Waist circumference (cm)		61.4 cm	10.1		59.9 cm	9.5	0.050^†^

Abbreviation: SD, standard deviation.

^†^Kruskal–Wallis.

^∗^
*p*‐value < 0.05.

Both groups are comparable in weight, BMI, TMI, weight z‐score, and body fat percentage, with slight differences in age, sex distribution, and height.

The overall rate of overweight and obesity in our sample was 37.9%. When assessing the distribution of overweight and obesity among the different schools (public, subsidized, and private), we found a significantly higher proportion of overweight and obesity in public schools than in subsidized schools and a higher proportion in subsidized schools than in private schools (*p* = 0.001, Table 3).

**TABLE 3 tbl-0003:** Percentage of overweight and obesity by type of school.

	Type of school			
	Public	Partially subsidized	Private	Total
Adequate BMI, *N* (%)	107 (51.4)	153 (66.8)	86 (71.7)	346 (62.1)
Overweight, *N* (%)	46 (22.1)	41 (17.9)	20 (16.7)	107 (19.2)
Obesity, *N* (%)	55 (26.4)	35 (15.3)	14 (11.7)	104 (18.7)
Overweight + obesity (%)	48.6%	33.2%	28.3%	37.9%
Total (N)	208	229	120	557

*Note:* Pearson chi‐square: *x*
^2^(4) = 19.1993; *p* = 0.001.

Abbreviation: BMI, body mass index.

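### The stated sample size of 286 children per arm does not follow from the stated inputs, which give 64 per arm, or 76 with attrition

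*Protocol article*

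**What the plan says.** All inputs stand in one sentence of section 2.5 of the protocol article. The result is "Sample size (286 kids in each arm of the study) was estimated using" a two-independent-means method, "assuming an effect size of 0.75 BMI units (SD = 1.5), 80% power", with two-sided alpha 0.05 and expected attrition of 15%. The same section says that the calculation was made at the individual level and that it took no account of the ICC. It concedes that "The absence of this adjustment may have led to an overestimation of statistical power".

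The text does not say what the SD of 1.5 refers to. Section 2.4 names the change in BMI as the primary outcome, and section 2.5 plans models adjusted for the baseline value. Table 2 (section 3.1) gives baseline BMI SDs of 3.4 in control and 3.2 in intervention. Section 3 reports the enrolment: "298 in the intervention group (from 5 schools) and 259 in the control group (from 8 schools").

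**The concern.** A difference of "0.75 BMI units (SD = 1.5") is a standardised effect of 0.5, for which 80% power needs about 64 per arm. A target of 286 cannot come from that calculation. This is the trial's only sample-size justification, and it concerns the primary outcome. Because the stated inputs and the stated result contradict each other, a reader cannot tell which effect the trial was sized to detect, or against what variability. The limitation in section 2.5 warns of too much claimed power, while the stated inputs at 286 per arm give far more than 80% at the individual level. So the caveat does not tell the reader which way the error runs.

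**Working it through.** **Inputs (section 2.5).** Difference 0.75; SD 1.5; power 80%; two-sided alpha 0.05; attrition 15%; no clustering. Allocation is 1:1 by participant (section 2.2).

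**1. Attempt to reproduce 286.** n per arm = 2(z₀.₉₇₅ + z₀.₈₀)² × SD² / difference² = 2 × (1.960 + 0.842)² × 2.25 / 0.5625 = 62.8, so 63. The t-test solution is 63.8, so 64. Dividing by 0.85 gives 63/0.85 = 74.1, so 75, and 64/0.85 = 75.3, so 76. The ratio 286/76 is 3.76 and 286/75 is 3.81. The figure is not reproduced.

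**2. Power at 286.** With 286 per arm, or 243 after 15% loss (286 × 0.85), and a standardised effect of 0.5, two-sided t-test power is above 99.9%.

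**3. Usual variants, per arm.**
- Two-sided with power 90%, 95% or 99%, plus attrition: 100, 123, 173.
- One-sided with power 80% to 99%, plus attrition: 59 to 150.
- Attrition as n × 1.15: 73 or 74.
- SD of 1.5 × √2, plus attrition: 149.
- 286 read as a total: the total would be 150 to 152.

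None comes near 286.

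**4. What would give about 286.**
- Difference 0.75 with SD 3.2 and no attrition: 285.8.
- Difference 0.75 with SD 2.95: 242.9, and 242.9/0.85 = 285.7.
- SD 1.5 with difference 0.35 and no attrition: 288.
- SD 1.5 with difference 0.38: 244.6, and 244.6/0.85 = 288.
- A design effect of about 3.8: with 557/13 = 42.8 children per school, ICC = (3.81 − 1)/(42.8 − 1) ≈ 0.067. Section 2.5 says that no such adjustment was made.

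**5. What SD 1.5 could be.** As the SD of change it satisfies 1.5 = 3.3 × √(2(1 − r)), which gives a baseline to follow-up correlation r of about 0.90 (3.3 is midway between the two SDs in Table 2). With r = 0.90 the baseline-adjusted residual SD is 3.3 × √(1 − 0.81) = 1.44. The article gives no correlation, so r is an assumption.

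**6. The realised design.** Children after 15% loss: 298 × 0.85 ≈ 253 in 5 schools (about 51 per school) and 259 × 0.85 ≈ 220 in 8 schools (27.5 per school). SE² = SD² × [(1 + (m_I − 1)ICC)/n_I + (1 + (m_C − 1)ICC)/n_C]. For SD 1.5 and ICC 0.05: 2.25 × (3.48/253 + 2.325/220) = 0.0547, so SE = 0.234 and 0.75/SE = 3.2. Power is from the noncentral t with 13 − 2 = 11 df. The ICC values are assumptions.

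| ICC | Power, SD 1.5 | Detectable difference, SD 1.5 | Power, SD 3.2 (bound) |
|---|---|---|---|
| 0.01 | 99% | 0.50 | 51% |
| 0.02 | 96% | 0.56 | 42% |
| 0.05 | 83% | 0.72 | 28% |
| 0.10 | 62% | 0.93 | 19% |

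Power is for a difference of 0.75; the detectable difference is at 80% power. Using 9 df, to allow for the school-type strata, lowers power by at most about 2 percentage points. The SD 3.2 column ignores the planned baseline adjustment.

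**The case against.** The strongest reply is that the mismatch harms nothing. On the stated inputs 286 is more than enough, enrolment is over, and the planned analysis accounts for clustering. The article also already says that power may be overstated and the sample small. Much of this stands. No design decision changes, the estimand and the analysis are untouched, and a null result would be read from its estimate and confidence interval, which do not use 286. A reader might infer that a null result could not be interpreted; the documents do not support that.

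Other stronger readings also fail:
- A reader who sees that SD 3.2 returns 286, and that Table 2 has an SD of 3.2, might infer that the SD is the error. That match requires that the stated 15% attrition was never applied, and a smaller difference with SD 1.5 gives nearly the same number.
- A reader might take the SD 3.2 powers to show a badly underpowered trial. The outcome is change in BMI and the models adjust for baseline, so those powers are a pessimistic bound. An SD near 1.5 is consistent with a correlation of about 0.90.
- A reader might conclude that 80% power is out of reach for 5 versus 8 schools. With SD 1.5 the design has 80% power at an ICC between 0.056 and 0.057.

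What does not stand is that the admitted limitation covers the point. Omitting the ICC lowers the required number, so it cannot account for one that is 3.8 times too high.

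**Conclusion.** The point holds as an internal contradiction in section 2.5. The stated inputs give 64 per arm, or 76 with attrition, against a stated 286, so at least one of the SD, the difference or the 286 is misstated. This conclusion rests only on figures in the article and on standard formulas.

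Which figure is wrong cannot be settled from the document. Nor does the contradiction show that the trial has too few children, since the true power depends on an SD and an ICC that the article does not fix. With SD 1.5 and assumed ICCs of 0.01 to 0.10, power for 0.75 is about 99% to 62%. If the SD were 3.2 with no gain from baseline adjustment, it would be about 51% to 19%. The 80% statement should not stand as written.

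**What to change.** In section 2.5:

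1. State whether the SD of 1.5 is that of BMI, of the change in BMI, or of the residual after baseline adjustment.
2. Correct whichever of the SD, the difference or the 286 is wrong, so that the three agree with 80% power and 15% attrition.
3. Replace the 80% statement with the power or minimum detectable difference of the realised design: 5 versus 8 schools, 298 and 259 children less 15%, 9 to 11 df. Give it over a stated ICC range, for example 0.01 to 0.10, labelled as assumed.
4. Note that the control arm, at 259, is below the 286 target.

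The cost is one recalculation and a few sentences, with no extra enrolment and no change to the analysis. The only downside is that the stated power may become less favourable.

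### The 80% power comes from an individual-level calculation and is not restated for the 5 v 8 school trial; because 286 does not follow from its inputs, the overstatement cannot be sized

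*Protocol article*

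**What the plan says.** Section 2.5 (Statistical Analysis) of the protocol article sets 286 children per arm, "assuming an effect size of 0.75 BMI units (SD = 1.5), 80% power", with two-sided alpha 0.05 and 15% attrition. It says that "the sample size calculation was initially performed at the individual level using a two independent means approach", accepts that the cluster design calls for the ICC, and adds: "The absence of this adjustment may have led to an overestimation of statistical power, and this is recognized as a limitation". The remedy it offers lies in the analysis: mixed-effects models or cluster-robust standard errors with children nested in schools. It gives no ICC, design effect, revised power or detectable difference.

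Section 3 (Results) reports what was enrolled: "298 in the intervention group (from 5 schools) and 259 in the control group (from 8 schools"). The primary outcome is change in BMI (section 2.4), and the models adjust for baseline value and school type (section 2.5).

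**The concern.** The only power figure in the article belongs to a trial that randomises children one by one. This trial randomises schools, and there are 13 of them. Between-school variation adds ICC × (1/5 + 1/8) to the variance of the treatment difference (in units of SD²), and more children per school cannot reduce that term. Mixed models or robust standard errors make the test honest about clustering, but they do not restore power.

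The article says power may be overstated but not by how much. The size matters when the outcome results, which are to be reported separately, are interpreted. A null result could be taken as evidence against an effect of 0.75 BMI units because 80% power was declared, or dismissed as underpowered because clustering was ignored. The article gives no basis for choosing between these.

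**Working it through.** **Inputs from the article.** Difference 0.75, SD 1.5, 80% power, two-sided alpha 0.05, 15% attrition, 286 per arm (section 2.5). Enrolled: 298 children in 5 schools and 259 in 8 (section 3). Baseline BMI SD 3.4 control and 3.2 intervention (Table 2).

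**Assumed.** ICC 0.01 to 0.10; equal school sizes within arm unless stated; attrition even across schools.

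**Step 1: the article's own figure.** n per arm = 2 × (1.960 + 0.842)² × SD² / difference².
- SD 1.5: 62.8, so 63 (64 by the t-based formula). With attrition, 64 / 0.85 = 75.3, about 75. Using 63 × 1.15 gives about 73. None of these is 286.
- After 15% loss, 286 leaves 243 per arm, and 243 / 63 = 3.9 times what the stated inputs need. The article does not present this as an allowance for clustering.
- SD 2.95 gives 243, and 243 / 0.85 = 286. An effect of about 0.38 with SD 1.5 gives nearly the same number, because the standardised effect is the same (0.75 / 2.95 = 0.25; 0.38 / 1.5 = 0.25). The article does not say which, if either, was used.

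**Step 2: power for the trial as enrolled.** After 15% attrition, 298 × 0.85 = 253.3 and 259 × 0.85 = 220.2 children.

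Variance = SD² × [ICC × (1/5 + 1/8) + (1 − ICC) × (1/253.3 + 1/220.2)]

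Example, SD 1.5 and ICC 0.05: 2.25 × [0.05 × 0.325 + 0.95 × 0.00849] = 0.0366 + 0.0181 = 0.0547, so SE = 0.234. About two thirds of the variance is the school term. Power comes from the noncentral t with 13 − 2 = 11 df. The effect detectable with 80% power is about 3.09 × SE.

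| ICC (assumed) | Variance relative to no clustering | SD 1.5: power for 0.75 | SD 1.5: detectable effect | SD 2.95: power for 0.75 | SD 2.95: detectable effect |
|---|---|---|---|---|---|
| 0.01 | 1.4 | 99% | 0.50 | 57% | 0.98 |
| 0.03 | 2.1 | 92% | 0.62 | 41% | 1.22 |
| 0.05 | 2.9 | 83% | 0.72 | 32% | 1.42 |
| 0.10 | 4.7 | 62% | 0.93 | 21% | 1.82 |

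**Step 3: where 80% is lost at SD 1.5.** The crossing is at ICC 0.057 on 11 df. It is 0.053 on 9 df, which allows for two school-type terms. If school sizes vary with an assumed coefficient of variation of 0.5, it is about 0.045 on 11 df. Using 9 df instead of 11 lowers the tabulated powers by at most about 2 points.

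**The case against.** The strongest reply is that the authors already disclose the omission, directly after the calculation, and commit every outcome analysis to a method that respects clustering. On the only SD they state, the enrolled sample keeps 80% power at each of the ICCs 0.01, 0.03 and 0.05, because 286 is nearly four times what those inputs require. Enrolment is complete, so no recalculation can add schools, and the planned models will give a confidence interval that shows what a null result excludes.

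Much of this stands. A reader might infer that the trial is underpowered; the article does not support that. The low figures need an SD near 3, which the article never states as a planning value and which resembles the cross-sectional baseline SD of 3.2 to 3.4. The analysed outcome is BMI change, adjusted for baseline. If the baseline to follow-up correlation were 0.90 (an assumption), 3.3 × √(1 − 0.81) = 1.44, close to the stated 1.5. At 0.80 it would be 1.98, and power 89/73/60% at ICC 0.01/0.03/0.05.

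What the reply does not remove is that the disclosure gives a direction without a size, and that the reassuring reading depends on an SD that does not lead to the stated sample size.

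**Conclusion.** The point holds in a limited form. The 80% is not a property of the design that was run, no figure replaces it, and 286 cannot be derived from the inputs beside it. So neither reading is supported: that power is comfortably above 80%, or that it is well below.

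At the stated SD of 1.5, power for 0.75 BMI units runs from 99% at ICC 0.01 to 62% at ICC 0.10, crossing 80% at an ICC of roughly 0.045 to 0.06 depending on school-size variation and degrees of freedom. If the working SD was about 2.95, power is 57% at ICC 0.01 and 32% at 0.05; this is the pessimistic end. All of these rest on assumed ICCs, 15% attrition and a school-level t test. Adjustment for baseline and school type could lower both the SD and the ICC, by an amount the article does not give. The omission itself is disclosed; what is missing is its size and a sample size that agrees with its inputs.

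**What to change.** 1. Reconcile 286 with its inputs: state the SD, effect and any inflation that were actually used.
2. Replace the 80% statement by the effect detectable with 80% power for 5 v 8 schools, using the actual unequal school sizes and a t reference on about 9 to 11 df.
3. Use the SD and ICC of the outcome to be analysed (BMI change or baseline-adjusted BMI, conditional on school type) and show a stated range of ICCs. The baseline BMI ICC within school type can be estimated from data in hand, but serves only as a rough guide: it is on a different scale from the adjusted outcome, and 13 schools estimate it imprecisely.
4. Say that a null result will be read from the cluster-adjusted confidence interval, not against 80% power.

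The cost is one recalculation and a few sentences, with a stated figure that may be less favourable. No extra schools or children are needed.

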### 2.2. Participants and Randomization Process

Boys and girls aged 6–10 years (1^st^ to 4^th^ grades of primary school) from public, state‐subsidized, and private schools on the island of Gran Canaria, Canary Islands, Spain, were recruited. The selection of schools was based on convenience. After obtaining a list of schools from contacts with the local diabetic association and members of the team, the project was explained and schools were invited to participate. After obtaining the consent from several schools, the inclusion in both arms of the study was randomized with a 1:1 ratio (even though we performed cluster randomization, the aim was to have a 1:1 participant ratio, not a 1:1 classroom ratio), and the parents of the students in the aforementioned classes were invited to participate. Finally, those children whose parents consented to their participation were included. To randomize the participant schools, we employed a stratified cluster randomization approach. First, we categorized schools into three types: public, private, and subsidized. In Spain, type of school (public, subsidized, or private) is a strong indicator of socioeconomic background, as documented in previous national studies. This classification has therefore been used as a proxy for SES in the current analysis (each type of school represents a different SES, with a spectrum ranging from the lowest SES in the public schools, to the highest in the private ones [11]). Although randomization was stratified by school type (public, subsidized, and private) to account for socioeconomic differences, perfect balance between intervention and control groups was not achieved. This was due to variability in school sizes and the decision to prioritize a 1:1 ratio of participants rather than number of schools. This approach was chosen to preserve statistical power while maintaining the integrity of cluster randomization.

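### At least one school type has a single intervention school, so the SES interaction cannot be tested reliably with the cluster-robust errors that the plan permits

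*Protocol article*

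**What the plan says.** Section 2.5 (Statistical Analysis) plans subgroup work in one sentence: "Interaction terms will explore effect modification by SES and baseline BMI category". Sections 2.2 and 2.5 make school type the stand-in for SES, and section 2.2 gives it three levels: "First, we categorized schools into three types: public, private, and subsidized". Whole schools were allocated, so every child in a school is in the same arm.

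For clustering, section 2.5 offers two routes: "mixed‐effects regression models (or cluster‐robust standard errors) will be used to adjust for school‐level clustering". It names no small-sample correction for either, and sets significance at p < 0.05.

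The Results section gives the number of schools: "298 in the intervention group (from 5 schools) and 259 in the control group (from 8 schools". Table 2 in section 3.1 gives children by type and arm (control, intervention): public 87 and 121, partially subsidized 120 and 109, private 52 and 68. No cell is empty. The article does not say how many schools of each type are in each arm.

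**The concern.** An arm-by-type interaction compares the intervention effect between school types. It is estimated between schools, so its precision depends on the number of schools in each of the six arm-by-type cells, not on the number of children. Five intervention schools spread over three types leave very few schools per cell, and one cell must hold a single school. If that school does unusually well or badly for its own reasons, the data show the same pattern as a true SES effect.

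A valid standard error would at least show this as great uncertainty. The cluster-robust estimator does the opposite, because it learns about between-school variation in a cell only from differences among the schools in that cell. At stake is whether a chance difference between schools is read as the programme working differently by socioeconomic group. The interaction with baseline BMI category varies within schools and is not part of this point.

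**Working it through.** **Inputs from the article.** 13 schools (5 intervention, 8 control), the six cell sizes in Table 2, and SD 1.5 (section 2.5). **Assumed, because not given:** the split of schools over types, a control split of 3/3/2, and ICC 0, 0.02 or 0.05. The plan gives no figure for this interaction that could be reproduced.

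**1. Schools per type.** Five schools over three non-empty types (public/subsidized/private) can split six ways: 3/1/1, 1/3/1, 1/1/3, 2/2/1, 2/1/2, 1/2/2. Each has at least one type with one intervention school, and three of the six have two such types. This step needs no assumption.

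**2. Cluster-robust variance of a cell mean.** In a model with arm fully crossed with type and no covariates, the estimated variance of a cell mean is, up to the finite-sample factor,

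(1/n²) × Σ over schools in the cell of (sum of that school's residuals)².

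Residuals in a cell sum to zero. If the cell is one school, its only term is 0² = 0, so the cell's standard error is exactly zero.

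With age, sex and baseline BMI added, the simulated standard error of a one-school private intervention cell (n = 68, ICC 0.05) averaged about 0.012. The true value is about 1.5 × √(0.05 + 0.95/68) = 1.5 × √0.0640 = 0.38. Covariates therefore do not repair it.

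The interaction contrast adds the variances of four cells. Its standard error is therefore too small, but not zero.

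**3. False-positive rate, cluster-robust joint test.** No true interaction, nominal 5%, 13 schools, factor G/(G-1) × (N-1)/(N-k), 2,000 runs per setting:

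| Intervention split (public/subsidized/private) | ICC 0 | ICC 0.02 | ICC 0.05 |
|---|---|---|---|
| 2/2/1 | 31% | 34% | 35% |
| 1/2/2 | 29% | 33% | 33% |
| 3/1/1 | 35% | 41% | 45% |
| 1/3/1 | 34% | 41% | 44% |
| 1/1/3 | 30% | 38% | 41% |

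A second simulation on the same assumptions gave 27-46%. The inflation is present at ICC 0, so it does not depend on the unknown ICC.

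**4. Mixed model (maximum likelihood, 300 runs per setting).** The one-school cell now has a standard error of about 0.19-0.25, so it is no longer near zero. The joint test still rejects too often:

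| Split | ICC | z/chi-square | F(2,7) |
|---|---|---|---|
| 2/2/1 | 0.02 | 18% | 9% |
| 2/2/1 | 0.05 | 26% | 14% |
| 3/1/1 | 0.02 | 20% | 10% |
| 3/1/1 | 0.05 | 27% | 14% |

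**5. School-level analysis.** With 13 schools and 6 cells, 13 − 6 = 7 residual df remain, and the interaction uses 2. The F(2,7) test on school-level results rejected about 3-6% in simulation, which is close to nominal. It takes between-school variance from all cells and applies it to the one-school cell as well.

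**The case against.** The strongest reply has four parts.

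- **The mixed model is named first; cluster-robust errors are an alternative in brackets.** True, and the mixed model removes the near-zero cell. But the alternative is expressly allowed, and the mixed model with default inference is still well above 5%.
- **Exact zero variance is not what the planned model gives.** This stands. Section 2.5 adjusts for baseline values, age and sex, so the cell's error is close to zero rather than zero, and the interaction's own error is understated rather than absent. The article also does not fix school type as three unordered categories in the interaction. An ordered term lowers the false-positive rate to 12-30%, still above nominal.
- **The analysis is exploratory, and the Discussion already urges caution over the imbalance of school types.** That limits the claims that can be made, but does not correct the error bars. The limitations do not mention how few schools lie behind each arm within a type.
- **Small-sample degrees of freedom belong in an analysis plan.** Often so. Here, however, the article itself fixes the SES variable, the interaction and a permitted variance method that fails with five intervention schools.

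A reader might also infer that a false SES finding is likely and will be a prominent result. The documents do not support this. The simulated rates are below one half, and the gradient that the article stresses is baseline prevalence by school type, not a difference in intervention effect. Nor is ordinary regression that ignores schools a planned option, since section 2.5 commits all outcome analyses to models that respect clustering.

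**Conclusion.** The point holds for the SES interaction. That one type rests on a single intervention school follows from the article's own counts, and no model can separate that school's deviation from an effect of its type. Under the permitted cluster-robust errors, the joint test at nominal 5% rejects about 27-46% of the time when there is no interaction. Under the mixed model with default inference the figure is about 18-27%.

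These rates are illustrative. They rest on assumed school splits and ICC 0-0.05, and the mixed-model figures come from only 300 runs per setting. The direction and rough size were the same in every split tried.

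The calculation says nothing about the main intervention effect. Because the analysis is exploratory and no confirmatory claim depends on it, this is a correction that should be made rather than a threat to the trial's primary result.

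**What to change.** Add a sentence to section 2.5, or to the analysis plan, limited to the arm-by-school-type interaction:

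- Do not use cluster-robust standard errors for this term.
- Use a school-level analysis with the F test on 2 and 7 df, which held its level in simulation. As second choice, use a mixed model with small-sample degrees of freedom, bearing in mind that F(2,7) on a maximum-likelihood fit still rejected 9-14%.
- Report the estimate and interval as descriptive, with the number of schools in each arm and type beside it, and say which cells rest on one school.

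The cost is one sentence and a wider interval, which reflects how little these schools can say about SES differences.

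Merging types into public versus the rest is not required. If the lone intervention school is public, that contrast still rests on one school, and it gives up one of the three strata used in randomization.
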